### Exclusion Criteria

The exclusion criteria are as follows: (1) cervical spondylosis of the nerve root type or spinal cord type and severe spinal stenosis; (2) a history of spinal surgery or severe spinal trauma; (3) a history of congenital variation or malformation of an unstable cervical vertebral structure; (4) dizziness or vertigo caused by other diseases diagnosed by specialized examinations such as those performed by cardiovascular, otolaryngology, and neurology departments; (5) imaging findings, including spinal infection, fracture, tumor, tuberculosis, severe spinal deformity, severe osteoporosis, ankylosing spondylitis, and osteitis deformans; (6) severe primary diseases of the endocrine system, cardiovascular system, and autoimmune system, and tumor or mental illness; (7) pregnancy and breastfeeding; and (8) no acceptance of cervical manipulation therapy.

### Withdrawal Criteria

The withdrawal criteria are as follows: (1) severe or intolerable adverse reactions during the observation process; (2) persistent or progressive symptoms and no suitability for participation in the trial; (3) risk of health damage (such as sudden serious complications); and (4) voluntary withdrawal or interview miss for other reasons.

### Sample Size

The sample size calculation is based on our previous clinical research in patients with cervical spondylosis of the nerve root type, using the same primary outcome instrument. The efficiency of SCRM is 89.5%, while that of BCM is 54.6%. The sample size calculation formula is as follows:

The α is .05 and 1–β is .90. According to estimations, 48 participants per group are needed considering that this is a long-term follow-up that is expected to have a dropout rate of no greater than 20%.

### Randomization and Allocation

The randomization schedule will be prepared by the Institute of Traumatology, Shi’s Center of Orthopedics and Traumatology, Shuguang Hospital Affiliated to Shanghai University of Traditional Chinese Medicine. The specific randomization number lists will be computer-generated using IBM SPSS 22.0 (IBM Corp) and concealed from the screeners, assessors, and patients by a specialized staff member who is not involved in the study. Within a set of randomly generated numbers, odd numbers will be attributed to the SCRM group, while even numbers will be attributed to the BCM group. Subsequently, all numbers and their respective group assignments will be documented on a card and securely sealed within opaque envelopes. These envelopes will be labeled with sequential numbers corresponding to the patients and entrusted to the screeners who bear the responsibility of participant screening. Once a patient is successfully enrolled, provides written informed consent, completes the baseline measurements, and is confirmed as an eligible participant, the sealed envelope will be transferred to the manual therapist. The manual therapist will unseal the envelope and administer the intervention (SCRM or BCM) based on the instructions provided on the card. The allocation list containing sensitive information will be kept confidential by specialized personnel who are not involved in participant recruitment or outcome assessment. This information will not be disclosed to the data analysts or outcome assessors.

### Blinding

Participants will be unaware of their group assignment and will remain unaware of receiving SCRM or BCM treatment. The outcome assessors will also be unaware of the randomization allocation and will not be involved in the intervention process. The manual therapists will not be able to be blinded owing to their involvement in performing the interventional protocols. However, they will not participate in the outcome measurements or statistical analyses and will be instructed to refrain from disclosing treatment details to the outcome assessors or participants. The statistician will remain blinded to the group allocation until the completion of the statistical analyses.

### Interventions

The techniques used in this study are SCRM in the experimental group and BCM in the control group. The two techniques are commonly used in clinical treatment and have established SOPs in Shanghai. All patients will receive treatment twice a week, with a 2-day interval between sessions, for a duration of 4 weeks. In addition, there will be a relaxation therapy step before the 2 techniques, after which the SCRM or BCM technique will be performed. The relaxation therapy will be performed as follows:

The patient assumes a seated position, while the manipulation therapist positions themselves behind one side of the patient’s body.One hand of the therapist provides support to the patient’s forehead, while the other hand employs pressing, pulling, and kneading techniques on both sides of the patient’s cervical spine, as well as the trapezius, sternocleidomastoid, and levator scapulae muscles, repeating these actions 3 times.Subsequently, the therapist applies pushing techniques along the line extending from the 7th cervical spine to the acromion, repeating this action 3 times.

The entire relaxation therapy session lasts approximately 10 minutes.

### SCRM Technique

The primary technological approach in SCRM involves applying pressure with the thumb on the spinous process, transverse process, or pedicle of the patient’s axis while simultaneously rotating the cervical spine in an effort to restore it to its original alignment. AJS is categorized into 8 distinct techniques, which are determined by the specific imaging characteristics of the atlantoaxial joint. Figure 2 shows the comprehensive classification of AJS according to X-ray findings. Each technique within these categories employs different SCRM methods. When there is a simple asymmetrical gap between the lateral mass of the atlantoaxial joint and the odontoid process, the spinous process of the axis remains aligned with the midline of the spinous process, yet the discrepancy in distance between the lateral mass of the left and right atlas and the dentate process is evident. If the left block displays a 2-mm greater distance compared with the right block, it falls under type A (left oblique type). Conversely, if the right block displays a 2-mm greater distance compared with the left block, it is classified as type B (right oblique type). When there is a simple misalignment of the axis spinous process relative to the midline of the spinous process, the distance between the lateral masses of the left and right atlas and the dentate process is either equal or exhibits a difference within a 2-mm range. However, the spinous process of the axis deviates from the midline of the spinal axis. If the spinous process of the axis is located at the left of the midline, it is classified as type C (left rotation type). Conversely, if the spinous process of the axis is located at the right of the midline, it is categorized as type D (right rotation type). The types can mix as follows: when type A merges with type C, it is referred to as type AC; when type A merges with type D, it is referred to as type AD; when type B merges with type C, it is referred to as type BC; and when type B merges with type D, it is referred to as type BD. The SOPs of SCRM according to the different types are presented below [18].

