### Diagnostic Criteria

The diagnosis of AJS is based on the Diagnostic Criteria for Traditional Chinese Medicine and the International Classification of Diseases 11th Revision (ICD-11), and several aspects are considered. First, the patient has a history of neck strain or injury and has a long-term habit of working or living with a low head. Second, the clinical manifestations are mainly vertigo, dizziness, headache, and soreness in the neck. Third, the cervical movement is mainly limited to the left-right rotation of the atlantoaxial joint. When performing palpation, the muscle tension around the atlantoaxial joint increases or small blocky or strip-shaped muscle nodules are felt, which may induce or exacerbate dizziness or vertigo. Fourth, cervical X-ray or CT shows an asymmetrical gap between the lateral mass of the atlantoaxial joint and the odontoid process, with a difference of more than 2 mm, along with the misalignment of the axis of the spinous process relative to the midline of the spinous process.

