### BCM Technique

The BCM technique does not differ depending on the type of AJS. The SOP of BCM for patients with AJS (all types) is as follows [18]. First, the patient assumes a seated position, and the manipulation therapist stands behind the patient’s left side. Second, the therapist manipulates the patient’s jaw by flexing their left elbow and applies pressure to the occipital area with their right hand, which is supporting the occipital bone with the right palm and supporting the other 4 fingers. Third, the therapist gradually rotates the patient’s head to the left until reaching the active limit position and then instructs the patient to relax their neck while continuing to rotate the head to the passive limit position using both hands. During this process, a momentary force is exerted to further facilitate the left rotation of the patient’s head, resulting in audible clicking sounds emanating from the neck. Fourth, the therapist performs the 3 steps on the right side of the patient. It is important to note that the therapist can freely select one side (left or right) of the patient for the procedure.

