##### Imaging Changes of Cervical CT

All participants will undergo cervical CT examination at visits 0, 1, and 6. Two radiologists will measure the distance from the lateral mass of the atlantoaxial joint to the dentate process and the distance from the axis to the midline of the spinous process. Each radiologist will measure each image 3 times, and the average of the 6 outcomes will be taken as the final result. The improvement rate will then be calculated based on the results. The calculation formula is as follows:

Improvement rate = ([distance at pretreatment – distance after treatment] / distance at pretreatment) 100

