### Limitations

For classification, AJS has been divided into 8 types. For the different types, the SCRM techniques are different, while the BCM techniques are the same. As the incidence rate of AJS is not high, it may be difficult to recruit patients with each type of AJS, who meet the statistical requirements, in a limited time. Therefore, we will not separate the different AJS types, but instead combine them to observe the difference in efficacy between SCRM and BCM. In the future, we will further extend our project timeline and recruit as many subjects as possible for each type of AJS, so that efficacy analysis can be conducted for different types of AJS.

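### The axis-to-midline CT improvement rate divides by a distance that is nominally zero in AJS types A and B, if such patients are enrolled, and has no stated minimum otherwise

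*Protocol article*

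**What the plan says.** - **Imaging Changes of Cervical CT (Secondary Outcomes).** All participants have CT at visits 0, 1 and 6. Two distances are measured, one of them "the distance from the axis to the midline of the spinous process". Two radiologists read each image three times, and "the average of the 6 outcomes will be taken as the final result". The outcome is then "Improvement rate = ([distance at pretreatment – distance after treatment] / distance at pretreatment) 100". There is no rule for a zero or very small denominator. The section does not say which of the two distances enters the formula, or whether the rate is computed per patient or on group means.
- **SCRM Technique.** In types A and B the left-right gap is unequal but "the spinous process of the axis remains aligned with the midline of the spinous process". In types C and D the reverse holds: the spinous process is off the midline and the gap is equal or differs by no more than 2 mm. AC, AD, BC and BD combine both features. Procedures are given for all eight types.
- **BCM Technique.** "The SOP of BCM for patients with AJS (all types) is as follows".
- **Limitations.** "we will not separate the different AJS types, but instead combine them to observe the difference in efficacy between SCRM and BCM".
- **Diagnostic Criteria, fourth item.** A gap difference above 2 mm is required "along with the misalignment of the axis of the spinous process relative to the midline of the spinous process". Inclusion criterion 1 makes meeting the diagnostic criteria a condition of entry.

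**The concern.** A percentage change needs a baseline well away from zero. For a patient whose spinous process is already on the midline there is nothing to correct. The pretreatment distance is then zero or a small amount of reading error, and the formula returns 0/0, division by zero, or one error divided by another. A few such values can dominate an arm mean.

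CT alignment is the trial's direct measure of whether SCRM restores the position of the joint, which is the technique's stated purpose. A summary governed by patients with nothing to correct could hide a real difference between the arms. The protocol fixes this formula itself, and it fails in a subgroup that the same protocol defines. That makes it more than a detail left to an analysis plan.

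**Working it through.** The plan gives no figure for this outcome, so there is none to reproduce.

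**1. Which types can enter?** Set the type definitions against the fourth diagnostic item:

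| Type | Gap difference above 2 mm | Spinous process misaligned | Meets the item read literally |
|---|---|---|---|
| A, B | yes | no | no |
| C, D | no | yes | no |
| AC, AD, BC, BD | yes | yes | yes |

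The literal criterion leaves four of the eight types, while SCRM Technique, BCM Technique and Limitations provide for all eight. The document does not settle which applies.

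**2. One aligned patient.** Take 0.2 mm read before treatment and 0.8 mm after, with no true change. The rate is (0.2 − 0.8)/0.2 × 100 = −300%. The same 0.6 mm shift on a 4 mm baseline would be −0.6/4 × 100 = −15%.

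**3. Distribution of the rate in aligned patients.** Suppose the two values are sizes of independent zero-mean normal errors with equal SD.
- The rate is 100 × (1 − |e1|/|e0|). Its distribution does not depend on the SD, so smaller error does not help.
- The median is about 0% and the 5th percentile about −1170%. There is no finite mean.
- P(rate < −100%) = P(|e1|/|e0| > 2) = 1 − (2/π) arctan 2 = 29.5%.
- If instead each of the six readings is an unsigned distance with its own independent error, their average stays away from zero. The rate then has mean −11%, SD 56 points and 5th percentile −114%. That is milder, but still only noise.

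**4. Effect on the comparison of arms.** Every input here is an assumption except the sample size and dropout.
- 39 analysed per arm (48 × 0.8 = 38.4, rounded up).
- True reduction in deviation 60% v 35%, patient SD 25 points.
- Misaligned patients: mean deviation 4 mm, SD 1.2, minimum 1. Types A/B: true deviation 0.
- Two-sided P<.05, 1500 simulated trials per setting.
- Compared: a t-test on the per-patient rate, and a linear model of the post-treatment value in mm on arm and visit-0 value.

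| Share A/B, error SD | Power of the rate: one unsigned error-prone value | Power of the rate: mean of six unsigned readings | Power of adjusted mm (both error models) |
|---|---|---|---|
| 25%, 0.5 mm | about 6% | about 45-48% | about 85-94% |
| 10%, 0.5 mm | about 27% | about 77% | about 92-97% |

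At 25% A/B the estimated difference has the wrong sign in about 38% of trials under the first error model and 3-4% under the second.

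With no A/B patients and error SD 0.5 mm, the first model gives about 91% for the rate v 95% for adjusted mm. At 1.0 mm it gives about 45% v 79%, while the six-reading model shows no material loss.

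**5. A second set of assumptions.** Take 48 per arm, offsets of 2-5 mm, a true improvement of 40% and error SD 0.3 mm, with one unsigned value per visit. The median arm mean is 39.5% with no A/B patients, 26% with 10% and −7% with 25%. The typical patient-level SD within an arm rises from 11 to about 69 and then about 186 points.

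**The case against.** The strongest reply is that types A and B are not eligible. The fourth diagnostic item asks for both features, inclusion criterion 1 applies it, and the four types that remain all have a real offset. This is a fair literal reading, and on it the nominally zero denominator disappears. It does not close the point, for two reasons. Three other sections treat all eight types as trial patients. And the 2 mm floor applies to the gap, not to the spinous deviation, for which no minimum is stated.

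Secondly, how the formula is applied is partly inferred. A ratio of group means would be finite. Statistical Analysis names no test specific to this rate, and the pooling sentence in Limitations speaks of efficacy, not of CT. All of that stands. The per-patient reading is the more natural one, because the formula follows directly on each patient's averaged result, but the text does not say so.

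Thirdly, the size depends on the error model and the test. Under the harsher error model, a rank test on the same percentages has about 59% power at 25% A/B and 84% at 10%. The 25% share (two of eight types, equally frequent) has no support in the document, and "aligned" carries no tolerance in mm, so a small real offset is possible.

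A reader might infer that this outcome certainly has almost no power, or that the whole imaging assessment fails. The document supports neither. The figure of about 6% needs A/B patients to be enrolled in that share, a single error-prone value per visit, and a t-test on per-patient rates. The lateral-mass distance is also measured, and its asymmetry is present in types A and B. Types C and D would have the mirror problem only if the distance meant there is the left-right difference, which is not stated.

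**Conclusion.** The point holds conditionally. If type A or B patients are enrolled, the stated formula gives them no usable value for the axis-to-midline distance, and baseline-adjusted millimetres had more power in every such scenario examined. The shortfall runs from moderate (about 77% v 92-97% at 10% A/B with six averaged unsigned readings) to near-total (about 6% v 85-94% at 25% A/B with one error-prone value). If they are not enrolled, the shortfall is negligible to small at an error SD of 0.5 mm, and at 1.0 mm ranges from none to about 45% v 79%.

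These sizes rest on assumed type shares, offsets, treatment effects and measurement error, and on a per-patient rate compared by t-test. The conflict between the diagnostic criteria and the eight-type scheme rests on the text alone. The primary outcome, the sample size and the safety comparison are not affected. This is a modest point about one secondary outcome, worth acting on because the correction is cheap.

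**What to change.** 1. In Imaging Changes of Cervical CT, replace the improvement rate for the axis-to-midline distance by the deviation in mm at visits 1 and 6. Compare SCRM with BCM at each visit by a linear model with the visit-0 deviation in mm as covariate, over all enrolled patients. This works under either reading of eligibility.
2. If a percentage is still wanted, report it only descriptively, and only in patients whose visit-0 image shows misalignment. Take that classification from readings made before allocation is known, in both arms, so that the subset cannot depend on treatment.
3. Reconcile Diagnostic Criteria and Inclusion Criteria with SCRM Technique, BCM Technique and Limitations, so that it is clear which types the trial contains.

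The cost is the rewording of one secondary outcome and one regression per visit on measurements already planned. The downside is that the result is in mm rather than the familiar percentage, and that any percentage covers only the misaligned patients.

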**Figure 2 figure2:**
[figure not shown]
Comprehensive classification of atlantoaxial joint subluxation using X-ray. The green line indicates the distance between the lateral mass of the atlantoaxial joint and the odontoid process. The blue line indicates the axis line of the C2 spinous process. The yellow line indicates the midline of the spinous process. (A) Normal atlantoaxial joint; (B) Type A; (C) Type B; (D) Type C; (E) Type D; (F) Type AC; (G) Type AD; (H) Type BC; (I) Type BD.

For type A, the steps are as follows. First, the patient assumes a seated position, while the medical therapist stands behind the patient on the left side. The therapist’s left hand supports the patient’s forehead, specifically positioning the right thumb at the left transverse process of the patient’s axis. The remaining 4 fingers of the therapist’s right hand rest gently on the right side of the patient’s neck, resulting in a forward flexion of the patient’s neck by approximately 10°. Second, the therapist subsequently alters the position of their left hand, placing it on the patient’s right chin nodule, while maintaining the unchanged posture of the right hand. This adjustment allows the therapist to rotate the patient’s neck to its maximum range of active movement. Third, the therapist’s left hand persists in applying force to achieve the maximum range of passive movement in rotating the patient’s neck, while the right thumb maintains a fixed position. The patient is instructed to relax their neck. Subsequently, the left hand momentarily intensifies the force of left rotation, while the right thumb applies pressure to the transverse process in a rightward direction. This maneuver often elicits an audible “click” sound emanating from the neck, accompanied by a subtle sliding sensation beneath the therapist’s right thumb, and the procedure is considered concluded.

For type B, the therapist stands behind the patient’s right side, and the therapist’s right hand supports the patient’s forehead, specifically positioning the left thumb at the right transverse process of the patient’s axis. The remaining steps are the same as those for type A, except that they are all performed in the opposite direction.

For type C, the operation steps are the same as those for type A, while the right thumb of the therapist is fixed at the left spinous process of the patient’s axis.

For type D, the operation steps are the same as those for type B, while the left thumb of the therapist is fixed at the right spinous process of the patient’s axis.

For type AC, the operation steps are the same as those for type A*,* while the right thumb of the therapist is fixed at the left pedicle of the patient’s axis.

For type AD, the first operation steps are the same as those for type A, and the second operation steps are the same as those for type D*.*

For type BC, the operation steps are the same as those for type B*,* while the left thumb of the therapist is fixed at the right pedicle of the patient’s axis.

For type BD, the first operation steps are the same as those for type B, and the second operation steps are the same as those for type D*.*

### BCM Technique

The BCM technique does not differ depending on the type of AJS. The SOP of BCM for patients with AJS (all types) is as follows [18]. First, the patient assumes a seated position, and the manipulation therapist stands behind the patient’s left side. Second, the therapist manipulates the patient’s jaw by flexing their left elbow and applies pressure to the occipital area with their right hand, which is supporting the occipital bone with the right palm and supporting the other 4 fingers. Third, the therapist gradually rotates the patient’s head to the left until reaching the active limit position and then instructs the patient to relax their neck while continuing to rotate the head to the passive limit position using both hands. During this process, a momentary force is exerted to further facilitate the left rotation of the patient’s head, resulting in audible clicking sounds emanating from the neck. Fourth, the therapist performs the 3 steps on the right side of the patient. It is important to note that the therapist can freely select one side (left or right) of the patient for the procedure.

